## Abstract

**Background:**

Using functional foods in the prevention and treatment of type 2 diabetes mellitus (T2DM) has increased across the world owing to their availability, cultural acceptability, and lower side effects. The present study will aim to examine the impact of bitter almond (*Amygdalus communis* L. var. Amara) gum as a functional food on metabolic profile, inflammatory markers, and mental health in women with T2DM.

**Discussion:**

The present randomized controlled trial will aim to investigate any beneficial effects of bitter almond gum supplementation on the cardio-metabolic, immune-inflammatory, and oxidative stress biomarkers, as well as mental health in women with T2DM.

**Ethics and dissemination:**

The study protocol was approved by the Ethical Committee of the Tabriz University of Medical Sciences (IR.TBZMED.REC.1399.726).

**Trial registration:**

Iranian Registry of Clinical Trials (www.irct.ir/IRCT20150205020965N7)

**Supplementary Information:**

The online version contains supplementary material available at 10.1186/s13063-023-07085-7.

## Background

Type 2 diabetes mellitus (T2DM), a metabolic disorder characterized by imbalanced blood sugar levels, is thought to be precipitated by a combination of impaired insulin secretion and insulin resistance [1]. Ethnicity, genetic predisposition, obesity, low physical activity, and unhealthy diet are involved in the pathogenesis of T2DM [2]. In 2019, it was estimated that 463 million people are living with T2DM worldwide [3]. This number has almost tripled over the last two decades and is projected to reach 578 million by 2030 and 700 million by 2045 [4]. The prevalence of T2DM has risen dramatically in countries experiencing epidemiologic transitions, including Asia, the Middle East, and North Africa [5]. The economic costs attributable to T2DM are also considerable. T2DM direct health care expenditure was estimated to be US$760 billion in 2019 [3]. Thus, developing novel adjuvant therapies for the management of T2DM and its associated complications is vital. Recent progress in understanding the development and progression of diabetes has shown a strong association between hyperglycemia, oxidative stress, inflammation, gut microbiota, and T2DM [6].

Intracellular hyperglycemia increases reactive oxygen species (ROS) production, promotes advanced glycation end-product formation and activation of protein kinase C, and enhances polyol pathway flux. ROS stimulates the generation of inflammatory mediators and adhesion molecules, oxidized low-density lipoprotein (LDL) formation, and insulin resistance [7]. As oxidative stress can induce an inflammatory process, inflammation can also induce oxidative stress [8]. Following activation of the immune system, innate immune system cells pro-inflammatory produce cytokines and chemokines, which stimulate the production of reactive oxygen and/or nitrogen species. Pro-inflammatory cytokines activate macrophages to eliminate pathogens via the generation of ROS [9]. Increased inflammatory markers may be related to mental health conditions [10]. Depressive disorders and impaired mental health-related quality of life are more prevalent among people with T2DM [11]. The relationship between T2DM and depression is thought to be bidirectional because of similar underlying pathological features in these conditions, including inflammation [12]. Higher serum levels and expression of inflammatory and pro-inflammatory markers in depressed patients with T2DM have been reported [13].

The microbiome may play an essential role in the development of T2DM [14]; an increase in the abundance of Firmicutes and Actinobacteria and a decrease in the proportion of Bacteroidetes can result in an inflammatory cascade, insulin resistance, and oxidative stress [15]. Potential mechanisms include modulation of inflammation, increased intestinal permeability, changed glucose metabolism, altered fatty acid oxidation, synthesis, and energy expenditure [16]. Gut dysbiosis results in an increase in the leakage of bacterial products such as lipopolysaccharides (LPS) into the bloodstream [17]. LPS is recognized by Toll-like receptor 4 (TLR4), which is implicated in inflammation [18]. It has been shown that LPS activate intracellular pathways of c-Jun N-terminal kinase (JNK) and IκB kinase (IKK)-β [19]. Activation of JNK promotes the serine phosphorylation of insulin receptor substrate (IRS)-1, which inhibits normal signal transduction through the insulin receptor/IRS-1 axis, which inhibits its action, and leads to insulin resistance [20]. Activation of the IKKβ pathway induces the activation of nuclear factor (NF)-κB and enhances the expression of numerous pro-inflammatory mediators that are involved in insulin resistance [21]. Therefore, modulation of the gut microbiota can be considered a potential therapeutic strategy. One way would be to improve the gut microbiome by using prebiotics or probiotics. Prebiotics are non-digestible and fermentable fibers and sugars that promote the growth and/or activity of a beneficial gut microbiome [22]. Prebiotics increase the growth of beneficial bacteria such as lactobacilli and bifidobacteria, prevent the proliferation of harmful bacteria, and allow beneficial bacteria to produce short-chain fatty acids (SCFAs), including acetate, butyrate, and propionate [23]. These SCFAs decrease inflammation, improve intestinal membrane integrity, and increase the absorption of nutrients. A systematic review showed that prebiotics might improve metabolic and inflammatory biomarkers in adult women with T2DM [24].

Nowadays, the use of herbal medicine is proposed to be an adjunct to conventional antidiabetic treatments [25]. Medicinal plants contain glycosides, alkaloids, terpenoids, flavonoids, and carotenoids, which can exert antidiabetic effects [26]. Bitter almond gum is a key herb in Iranian medicine which is extracted from *Amygdalus scoparia* Spach. Remarkable in vitro antioxidant, antimicrobial, and antitumor effects of the water, methanol, and ethanol extracts of bitter almond kernels were demonstrated by Gomaa et al. [27]. Bitter almond gum increased the survival rate of *Lactobacillus acidophilus* La5 in tomato juice mixtures during fermentation, refrigeration, and exposure to gastric juice [28]. Bitter almond gum is an arabinogalactan polysaccharide that has prebiotic properties [29]. Bitter almond gum may have a favorable immune modulator effect possibly related to its prebiotic content [29]. To the best of our knowledge, there is only one study that evaluated the effect of bitter almond gum on metabolic parameters in overweight hyperlipidemic patients. In this study, bitter almond gum-enriched juice consumption significantly reduced body weight, body mass index (BMI), serum triglyceride (TG), hyperinsulinemia, and homeostatic model assessment for insulin resistance (HOMA-IR). We hypothesized that bitter almond gum, as adjuvant therapy, is able to improve metabolic, inflammatory, and oxidative stress biomarkers, as well as mental health in T2DM women.

## Methods/design

### Ethical consideration

The trial protocol is approved by the Tabriz University of Medical Sciences Ethical Committee (IR.TBZMED.REC.1399.726). The clinical trial number is IRCT20150205020965N7, which has been registered on the Iranian Registry of Clinical Trials (IRCT) website (www.irct.ir/IRCT20150205020965N7). This study will be conducted in accordance with the Declaration of Helsinki. Written informed consent will be obtained from all participants prior to study entry and after patient education about the study objective, process, schedule, potential risks, and benefits.

### Protocol amendments

Any changes in the study protocol will be reviewed and approved by all authors. If any major change is made to the protocol, additional ethical approval must be obtained from the Ethics Committee.

### Dissemination

The results of this experience will be published in a peer-reviewed journal.

### Safety assessments

The dosage to be administered in this clinical trial is within the recommended range based on the previous studies [30]. Moreover, documentation of all potential adverse events reported by the patients will be recorded by investigators from baseline through the follow-up period. If the reported adverse events are associated with the use of bitter almond gum, patients will be asked to stop taking the supplement, and they will be referred to a physician for therapy. Subjects with adverse events will be followed until the events will be resolved. Serious adverse events will be followed up to determine the final outcome. In addition, any possible negative effects will be notified to the ethics committee.

### Study design and participants

The proposed study is a randomized, triple-blind, placebo-controlled, parallel-group clinical trial with a superiority framework to deliver an intention to treat (ITT) to evaluate the efficacy of bitter almond gum on cardio-metabolic, immune-inflammatory, and oxidative stress biomarkers, as well as mental health, compared with a placebo in women with T2DM. The allocation ratio will be 1:1. The study will begin later this year, 2022. Women with T2DM will be recruited from clinics of the Tabriz University of Medical Sciences, Iran, through public announcement systems and doctor referrals. A trained nutritionist will be served to include participants until the target sample size is reached and the project supervisor will assign participants to intervention groups based on the randomization list. The research design is presented in Fig. 1. This clinical trial protocol is based on the Standard Protocol Items: Recommendations for Interventional Trials (SPIRIT) 2013 checklist (Additional file 1: SPIRIT checklist) [31]. The diagram of the study protocol and initial and ongoing participant recruitment is demonstrated in Table 1.

**Fig. 1 Fig1:**
[figure not shown]
Consolidated Standards of Reporting Trials (CONSORT) diagram

**Table 1 Tab1:**
[figure not shown]
Standard Protocol Items: Recommendations for Interventional Trials (SPIRIT) chart for the study process. The “X” is indicating what is done in the given period

*PPAR* peroxisome proliferator-activated receptor

### Eligibility of criteria

Women aged between 30 and 65 years and diagnosed with T2DM (fasting blood sugar (FBG) ≥126 mg/dl [32]) that satisfy the inclusion criteria will be recruited. The inclusion criteria will be considered as follows: diagnosed with T2DM at least 6 months, body mass index (BMI) > 25 and < 35 kg/m^2^, no weight changes during the last three months, use of glucose-lowering drugs (including sulfonylureas, glinides, biguanides, thiazolidinediones, dipeptidyl-peptidase 4 inhibitors, sodium-glucose transporter 2 inhibitors, alpha-glucosidase inhibitors, amylin mimetics, and incretin mimetic), dietary fiber intake of < 25 g per day, and propensity to take bitter almond gum supplement during the study. Patients will be excluded if they use insulin, glucocorticoids, laxatives, anti-obesity drugs, nonsteroidal anti-inflammatory drugs (NSAIDs), antidepressants, and antibiotics; take supplements including multivitamins, n-3 fatty acids, Ginkgo biloba, antioxidants, probiotics, and other prebiotics in the previous 3 months before the recruitment; have a history of weight loss or dieting in the last 6 months; have cancers and gastrointestinal, thyroid, heart, kidney, liver, lung, and infectious diseases; consume alcohol and smoke; and are pregnant or lactating.

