### Randomization and blinding

After obtaining the informed consent of the study participants, eligible subjects will complete a 2-week run-in period. During this time, patients will be requested to follow dietary and exercise advice according to recommendations for T2DM patients [33]. After the run-in period, the patients will be randomized to one of the two arms (bitter almond gum group or placebo group) in equal numbers, stratified by age and BMI. For stratified block randomization, random allocation software (RAS) will be used with block sizes of 2 and 4. Randomization will be performed by a third party that is not involved in this research. Block size will be concealed to all researchers until code-breaking. To enter a patient into the trial, one of the researchers will open the sequentially numbered sealed opaque envelopes. The study design is blinded to the main investigator, those who collect the data, the statistical consultant, and the participants.

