### Primary and secondary outcomes

Primary outcomes of the study will be FPG, glycosylated hemoglobin (HbA1c), and insulin. Secondary outcomes will include the lipid profile (total cholesterol (TC), high-density lipoproteins (HDL), low-density lipoproteins (LDL), TG), high-sensitivity C-reactive protein (hs-CRP), tumor necrosis factor-α (TNF-α), interleukin-1 (IL-1), interleukin-6 (IL-6), interleukin-10 (IL-10), interleukin-17 (IL-17), lipopolysaccharides (LPS), total antioxidant capacity (TAC), malondialdehyde (MDA), oxidative stress index (OSI), total oxidant status (TOS), superoxide dismutase (SOD), glutathione peroxidase (GSH-Px), catalase (CAT), soluble receptor for AGEs (sRAGE), carboxymethyl lysine (CML), pentosidine, 8-iso-prostaglandin F2α (8-iso-PGF2α), nitric oxide (NO), tryptophan (Trp), kynurenine (KYN), cortisol, glucagon-like peptide 1 (GLP-1), receptor for advanced glycation end products (RAGE), leptin, adiponectin, ghrelin, peroxisome proliferator-activated receptor (PPAR) gene expression, brain-derived neurotrophic factor (BDNF), endothelial cell adhesion molecules, plasminogen, cluster deference 4 (CD4), cluster deference 8 (CD8), anthropometric indices, blood pressure, dietary intake, and mental health. The following variables will be considered covariates: energy intake, weight changes, and the baseline values of glycemic indices, lipid profile, LPS, inflammatory and oxidative stress biomarkers, adipokines, and parameters related to mental health and the immune system. All variables will be measured at baseline and at the end of the study.

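### Entry requires glucose-lowering drugs but no period on an unchanged drug and dose, so recent drug changes can add avoidable noise to the glycaemic primary outcomes

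*Protocol article*

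**What the plan says.** The article's eligibility section lists its criteria in detail, several with time windows:

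- Diabetes: "diagnosed with T2DM at least 6 months".
- Weight and drugs, side by side: "no weight changes during the last three months, use of glucose-lowering drugs (including sulfonylureas, glinides, biguanides". The three months apply to weight. The drug criterion goes on to name nine classes and gives no duration.
- Supplements and prebiotics are excluded if taken "in the previous 3 months before the recruitment".
- Weight loss or dieting is excluded over six months.

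On outcomes: "Primary outcomes of the study will be FPG, glycosylated hemoglobin (HbA1c), and insulin". All variables are measured at baseline and at the end of the 8 weeks.

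Other sections bear on background treatment as follows:

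- In the 2-week run-in, "patients will be requested to follow dietary and exercise advice according to recommendations for T2DM patients". Drugs are not mentioned.
- Randomisation is "in equal numbers, stratified by age and BMI".
- The listed covariates are energy intake, weight changes and baseline values of the biomarkers. There is no medication term.
- The clinical assessment section records current medication use at baseline. It does not mention start dates or dates of the last change.

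**The concern.** The protocol controls weight, dieting and supplements over time before entry, but not the one background treatment that every participant must take and that acts directly on the primary outcomes. A woman diagnosed seven months ago whose drug was started or altered two weeks ago meets every stated criterion.

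Her baseline value may not yet reflect the new regimen, and her week-8 value may then differ from baseline whichever powder she receives. A mixture of settled and still-drifting women widens the residual variance. With 22 randomised per arm and 19 required, there is little room for avoidable noise. The sample size was set on LDL, which the outcomes section lists as secondary, so no spare power has been shown for the glycaemic primaries either.

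This is not a matter of article condensation: the criterion and its neighbours' windows are printed, and eligibility belongs in the protocol.

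**Working it through.** **1. Does any other provision fill the gap?**

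| Provision | What it covers | Requires an unchanged drug and dose? |
|---|---|---|
| Diagnosis at least 6 months ago | Time since diagnosis | No |
| Weight stable for 3 months | Weight | No |
| 2-week run-in | Diet and exercise advice | No |
| Strata | Age, BMI | No |
| Covariates | Energy intake, weight change, baseline values | No |
| Baseline medication record | Current use | No |

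None does.

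**2. Does baseline adjustment remove the problem?** Only in part. Take two women with the same baseline HbA1c, one settled on treatment and one recently changed. Their expected week-8 values differ, and the baseline value cannot tell them apart. If recently changed women also tend to have different baselines, ANCOVA absorbs some of the difference.

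**3. The plan's own figures.** The sample size section gives a 28.3 mg/dl difference in LDL, 90% power and 95% confidence (read as two-sided 5%), leading to 19 per group, raised to 22 for 15% drop-out. No SD is stated, so 19 cannot be reproduced independently. Solving n = 2(1.960 + 1.282)² SD²/28.3² for n between 18 and 19 gives an SD of about 26.2 to 26.9 mg/dl. For drop-out, 19/0.85 = 22.4 (23 rounded up) and 19 × 1.15 = 21.9 (22). At 15% loss, 22 × 0.85 = 18.7, so about 19 women per arm are analysable. None of this gives power for fasting glucose, HbA1c or insulin.

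**4. Illustration for HbA1c.** All three inputs are assumptions and none is in the documents:

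- share q with a recent change: 10-30%
- extra HbA1c shift d over 8 weeks in those women: 0.5-1.0 points
- residual SD without such changes: 0.7 points

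Variance inflation is V = 1 + q(1−q)d²/SD². It gives baseline adjustment no credit. Equivalent sample size per arm is 19/V. For power, take the effect that has 90% power at 19 per arm in a two-sided 5% two-sample t-test (1.081 SD) and divide it by √V.

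| q | d | V | 19/V | Power |
|---|---|---|---|---|
| 0.10 | 0.5 | 1 + 0.09 × 0.25/0.49 = 1.046 | 18.2 | 89% |
| 0.20 | 0.8 | 1 + 0.16 × 0.64/0.49 = 1.209 | 15.7 | 84% |
| 0.30 | 1.0 | 1 + 0.21 × 1.00/0.49 = 1.429 | 13.3 | 77% |

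**5. Chance imbalance is already inside these figures.** The SD of the between-arm shift from unequal numbers of recently changed women is √(2q(1−q)d²/19), which is 0.05, 0.10 and 0.15 points in the three rows. Without drug changes the standard error of the arm difference is 0.7 × √(2/19) = 0.227. Adding the shifts in quadrature gives 0.232, 0.250 and 0.271, whose squared ratios to 0.227 return the same V.

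**6. A second set of assumptions.** With the shift expressed in residual SDs (m), V = 1 + q(1−q)m², and a normal approximation at 19 per arm, power is 89.4% (q = 0.10, m = 0.5), 85.3% (0.20, 1.0) and 76.2% (0.30, 1.5). The range is similar, and equally conditional.

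**The case against.** The strongest reply is that the effect is conditional and may be negligible. The documents give no rate of recent drug changes. At the low end power moves by about one point, and 77% needs both upper assumptions at once. The 90% starting point is stated for LDL only, so for the glycaemic primaries it is hypothetical. The arithmetic covers HbA1c, not fasting glucose or insulin. The diagnosis-duration and weight-stability criteria will also keep out some recently changed women, and baseline adjustment recovers part of the loss. All of this stands, and it limits the size of the point. It does not close the gap, because none of these provisions requires a settled regimen.

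Three stronger readings are tempting and are not supported:

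- *The result would be biased.* Drug changes made before entry cannot depend on the allocated powder, so under randomisation the comparison stays unbiased.
- *Chance imbalance is a further harm that can produce a false gum effect.* It is the same added variance seen from another side. The test's estimated variance includes it, so the false-positive rate stays near nominal.
- *HbA1c will fall in these women.* A recent change may be a reduction, or a switch with little net effect. All that can be said is that values may still be drifting.

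**Conclusion.** The point holds as a loss of precision. The eligibility criteria as written admit women whose primary outcomes may still be moving because of a recent drug change, and nothing else in the protocol prevents or adjusts for it. Under the assumed inputs (10-30% of women, 0.5-1.0 HbA1c points, residual SD 0.7), residual variance rises by 5-43%, and a comparison that would have 90% power at 19 per arm has about 89% down to 77%. These figures show scale and do not estimate the power of this trial: a reader might infer that the trial's actual power drops to 77%, but the documents supply neither the inputs nor a starting power for any glycaemic primary. The change is worth making because it is inexpensive and cannot be applied to women once they have been randomised.

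**What to change.** Add to the inclusion criteria that glucose-lowering drugs and their doses have been unchanged for a stated period before enrolment. The three-month window that the protocol already uses for weight and supplements is the natural choice, but the length is for the sponsor to set. The criterion limits who enters and says nothing about what treatment a patient should receive.

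Collect the start date and the date of the last change for each glucose-lowering drug at screening. The present baseline record of current use cannot verify the criterion.

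Cost: a protocol amendment. The trial status section says that the trial has not started but that recruiting is already underway, so the new criterion would apply to women not yet randomised, including some who may already have been screened. Under the amendments section, ethics approval is needed if the change counts as major. Screening gains a few data items, and recruitment slows slightly because recently changed women wait or are not enrolled.

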### Randomization and blinding

After obtaining the informed consent of the study participants, eligible subjects will complete a 2-week run-in period. During this time, patients will be requested to follow dietary and exercise advice according to recommendations for T2DM patients [33]. After the run-in period, the patients will be randomized to one of the two arms (bitter almond gum group or placebo group) in equal numbers, stratified by age and BMI. For stratified block randomization, random allocation software (RAS) will be used with block sizes of 2 and 4. Randomization will be performed by a third party that is not involved in this research. Block size will be concealed to all researchers until code-breaking. To enter a patient into the trial, one of the researchers will open the sequentially numbered sealed opaque envelopes. The study design is blinded to the main investigator, those who collect the data, the statistical consultant, and the participants.

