### Statistical analysis

SPSS version 24.0 (SPSS Inc., Chicago, IL, USA) will be applied to analyze the data. Mean ± standard deviation (SD) or median (25th–75th percentile) and frequency (percentage) will be used to present quantitative and qualitative variables, respectively. The normality of our data will be assessed with the Kolmogorov-Smirnov test. Log transformation in the cases of non-normally distributed data will be done. In order to examine differences in qualitative and quantitative baseline variables between groups, we will apply the chi-square test and the unpaired Student *T*-test, respectively. To compare quantitative variables between groups, an analysis of covariance (ANCOVA) will be performed post-intervention. For within-group comparison, we will conduct the paired sample Student’s *T*-test or its nonparametric equivalent, the Wilcoxon test. To find the percentage difference, the absolute value of the change will be divided by the average of the values and multiplied by 100 [100 × (intervention values − placebo values)/placebo values]. *P* value < 0.05 will be considered statistically significant.

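### Randomisation is stratified by age and BMI, but the stated ANCOVA covariates include neither, so the tests are conservative and lose some power to the extent that these factors are prognostic

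*Protocol article*

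**What the plan says.** Under Randomization and blinding, the article allocates patients to the two arms "in equal numbers, stratified by age and BMI", and adds that "random allocation software (RAS) will be used with block sizes of 2 and 4". It gives no cut-points for either factor.

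Under Primary and secondary outcomes it names the covariates: "The following variables will be considered covariates: energy intake, weight changes, and the baseline values of glycemic indices, lipid profile, LPS", followed by "inflammatory and oxidative stress biomarkers, adipokines, and parameters related to mental health and the immune system". Age and BMI do not appear, and neither does any baseline anthropometric measure. The weight item is a change during the trial, so it does not stand in for baseline BMI.

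Under Statistical analysis: "To compare quantitative variables between groups, an analysis of covariance (ANCOVA) will be performed post-intervention". That section does not mention the strata.

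**The concern.** Stratified blocks force the arms to be alike on age and BMI, which makes the treatment estimate less variable. A model without these factors does not register that gain. It still counts the variation due to age and BMI as noise, so its standard error exceeds the real variability of the estimate. Intervals are then wider than they need to be, and the test rejects less often than its nominal level. In a trial of 44 patients this gives away precision that the design has already secured. Because the article names its covariates, the mismatch lies in what it states and not merely in what it leaves unsaid.

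**Working it through.** **Inputs from the article.** Stratification by age and BMI in blocks of 2 and 4, and 1:1 allocation. Sample size: 28.3 mg/dl difference in LDL change, 90% power, 19 per group, raised to 22 per group (44 in total). Significance level 0.05.

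**Assumptions.** Two-sided test; two levels per factor (2 x 2 strata) of equal expected size; each outcome's own baseline value in the model. R² is the share of the baseline-adjusted residual variance that the strata explain. The article gives no value for it, so it is varied.

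**Step 1: the plan's own figure.** No SD is stated, so 19 per group can only be solved backwards from n = 2(1.960 + 1.282)² SD² / 28.3² = 21.02 SD² / 800.89.
- SD 26.9: 21.02 x 723.61 / 800.89 = 18.99, rounded up to 19.
- SD 26.2: 21.02 x 686.44 / 800.89 = 18.02, rounded up to 19.

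The figure of 19 therefore implies an SD of about 26.2 to 26.9 mg/dl. The lower end of the standardised effect is 28.3 / 26.9 = 1.05. Below, this is taken as an effect in units of the baseline-adjusted residual SD.

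**Step 2: direction and approximate size.** With residual SD 1 and well-balanced strata:
- SE reported by the model without strata: √(4/44) = 0.302.
- True SE: √(4(1 − R²)/44), which is 0.286 at R² = 0.10 and 0.270 at R² = 0.20.
- Ratio: 1/√(1 − R²) = 1.05 and 1.12.

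Unfinished blocks leave some imbalance, so the real excess should be slightly smaller.

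**Step 3: simulation of the design, N = 44.** Each cell shows the model without strata, then the model with strata.

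| R² | Type I error | Power at 1.05 SD | Power at 0.8 SD (assumed) |
|---|---|---|---|
| 0 | 5.0% / 5.0% | 91.7% / 91.3% | 72.0% / 71.6% |
| 0.10 | 4.1% / 5.2% | 92.9% / 94.4% | 74% / 77% |
| 0.20 | 3.0% / 5.0% | 93.5% / 95.8% | 74% / 81% |

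At R² = 0.05 the type I error is 4.6% against 5.0%, and power at 1.05 SD is 92.5% against 93.3%.

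Without strata, the mean model SE against the true SE is 0.3031 / 0.2937 = 1.03 at R² = 0.10 and 0.304 / 0.2765 = 1.10 at R² = 0.20. This agrees with the type I errors: a normal test whose SE is 10% too large rejects when |Z| > 1.96 x 1.10 = 2.16, which has probability 3.1%.

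A repeat with 20,000 replicates at R² = 0.20 and 0.8 SD gave 74.4% against 81.5%, a loss of 7.1 points.

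**Step 4: only 38 patients analysed (2 x 19), R² = 0.20.** Type I error is 2.7% against 4.7%. Power is 88.2% against 92.6% at 1.05 SD, and 66% against 74% at 0.8 SD.

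**The case against.** **The loss is conditional and may be small.** This stands. Nothing in the article shows that age or BMI predicts week-8 values once the outcome's own baseline is in the model. Eligibility also confines age to 30 to 65 years and BMI to between 25 and 35, which narrows the range over which either could matter. At R² = 0 nothing is lost.

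**At the plan's own effect size the loss is only one or two points.** This is true with 44 patients. However, that effect is for LDL, which the outcome section lists as secondary. The article gives no effect size for FPG, HbA1c or insulin, so power above 90% cannot be presumed for them. The 0.8 SD column is a sensitivity case and not a figure from the plan.

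**Model terms may be settled in an analysis plan that is not shown.** In part this stands: the article condenses a longer document and does not call its list exhaustive. But it does commit to a named list, and that list leaves out the factors used to randomise.

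**Stronger readings that the documents do not support.** A reader might take the covariate list literally, count about 34 terms, and conclude that the model cannot be estimated.
- The article does not say that every listed variable enters every model. The families mirror the outcome panel, so adjustment of each outcome for its own baseline is the more natural reading.
- LDL is calculated from the other lipids and adds no separate term.
- Under the stated intention-to-treat analysis, even a count of 34 would leave 44 − 2 − 34 = 8 residual degrees of freedom.

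A reader might also infer that the intervals are invalid or that false positives increase. The error runs the other way: the intervals are conservative.

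**Conclusion.** The mismatch between the stratified design and the stated covariates is real. It affects efficiency and calibration, not validity. The type I error falls from 5% to about 4% if the strata explain 10% of the residual variance, and to about 3% if they explain 20%. The corresponding power loss with 44 patients is 1 to 2 points at about 1.05 SD, and 3 to 7 points at an assumed 0.8 SD. If the strata explain nothing, there is no loss. These sizes rest on two levels per factor, own-baseline adjustment and an assumed prognostic strength, none of which the article states. The change is still worth making, because adjusting costs almost nothing if the factors prove irrelevant.

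**What to change.** Under Primary and secondary outcomes and under Statistical analysis, state that each outcome is compared between arms by ANCOVA on its week-8 value, with treatment, that outcome's own baseline value, and the age and BMI stratification factors as covariates. The two factors should enter in the form used for stratification, and their cut-points should be given. Whether energy intake and weight change should also be adjusted for is a separate question that this point does not settle.

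**Cost.** A change of wording. Age and BMI must already be known in order to randomise. With two levels per factor, residual degrees of freedom fall from 44 − 3 = 41 to 44 − 5 = 39. If neither factor is prognostic, the simulated price is 0.4 power points (91.7% to 91.3% at 1.05 SD; 72.0% to 71.6% at 0.8 SD). The article reports that the trial has not yet started, so the change can be made before unblinding.
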